**7.2 Baseline Period**

At the beginning of a 7-day baseline period, the demography characteristics (sex, age, BMI, current employment status, education, marital status, and annual income), facial pain, and DC/TMD examination findings should be recorded.

The participant must be assisted with the provisioning and training of the TMD diary at the beginning of the baseline period. The TMD diary will be recorded daily during the baseline period. See **section 8.2.2** for further details on TMD diary. Participants compliance will be checked and at least 85% entries with the TMD diary should be attained. And an inclusion and exclusion criteria review based on TMD diary must be done at the end of baseline.

Each participant will also be provided with a participant identification card that states the participant identification number, the investigator’s name, and an emergency telephone number providing 24-hour service. The participant identification card should be returned to the investigator upon completion of the participant’s participation in the study.

At the allocation, participants will be randomly assigned (1:1) to either acupuncture group or sham acupuncture group. Additional examination of GCPS, JFLS-20, DASS-21, PSQI, PPT, and sEMG will be measured at the end of baseline. Laboratory tests, urine pregnancy test in female participants of childbearing potential vital signs, weight, and acupuncture expectancy scale will also be accessed at the end of baseline.

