**8.2.10 Acupuncture Expectancy Scale**

The acupuncture expectancy scale consists of an item measuring the expectation of improvement of illness due to acupuncture treatment. Patients will be asked to rate from 1 to 5 on a five-point Likert scale, with 1 indicating “Ineffective”, 2 indicating “May be ineffective”, 3 indicating “Unclear”, 4 indicating “May be effective”, 5 indicating “Effective” with the expected improvement as result of acupuncture.

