**Baseline period:**

• Eligibility criteria

• Demography Characteristics

• Disease history of temporomandibular disorder

• The clinical outcome assessment must be completed at the patient’s convenience before or after assessment of vital signs, weight

• Patients must complete the daily TMD diary entries prior to treatment

• The clinical outcome assessment completed in the clinic must be done before the treatment, including FDI, GCPS, JFLS-20, DASS-21, PSQI, PPT, sEMG, and acupuncture expectancy scale

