**12.6.2 Primary Analysis of the Primary Outcome**

The linear regression model will be applied for the primary outcome (change from baseline in mean weekly pain intensity at week 4). The model will include treatment as fixed effect; Sex, age, weekly pain intensity at baseline, TMD-specific medication as covariates. The LSM change from baseline with standard error (SE) was presented for each treatment group, and the LSM with 95% confidence intervals (95% CIs) for the treatment differences, and associated p-values will be provided.

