## 6.3 Demographics and Baseline Characteristics

Participant’s demographics and baseline characteristics, including age, gender, body-mass index, current employment status, education, marital status, annual income, and facial pain will be summarized for the ITT population. The baseline diary efficacy variables listed in **section 8.1**, jaw opening and movement measurement, GCPS total score, JFLS-20 total score, DASS-21 total score, PSQI total score, PPT, sEMG, and expectation assessment, will be summarized by treatment group for the ITT set.

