### 8.2.1 Primary Efficacy Analysis

The hypothesis testing for the primary analysis is:

*H_0_: δ_1_=δ_2_*

*H_1_: δ_1_≠δ_2_*

where δ1 and δ2 are the estimates of weekly pain intensity change from baseline to the last week of treatment for the acupuncture group and the sham acupuncture group respectively.

The primary efficacy endpoint was the change from baseline in mean weekly pain intensity at week 4, the main analysis was performed using an analysis of linear regression model adjusted for sex, age, weekly pain intensity at baseline, TMD-specific medication. The LSM change from baseline with SE was presented for each treatment group, and the LSM with 95% confidence intervals (95% CIs) for the treatment differences, and associated p-values will be provided. A corresponding sensitivity analysis will be performed on the PP set using a linear regression model as specified for the primary efficacy outcome on the ITT set.

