##### 8.3.1.2.7 ****Acupuncture Expectancy Scale****

The acupuncture expectancy scale consists of an item measuring the expectation of improvement of illness due to acupuncture treatment. Patients will be asked to rate from 1 to 5 on a five-point Likert scale, with 1 indicating “Ineffective”, 2 indicating “May be ineffective”, 3 indicating “Unclear”, 4 indicating “May be effective”, 5 indicating “Effective” with the expected improvement as result of acupuncture.

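### Pre-treatment acupuncture expectancy is collected but only tabulated; pre-specifying it as a covariate of the primary model is a cheap precision safeguard, not the repair of an error

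*Combined protocol and SAP*

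**What the plan says.** Protocol 12.6.2 fits treatment with "Sex, age, weekly pain intensity at baseline, TMD-specific medication as covariates". SAP 8.2.1 repeats that list: the model is "adjusted for sex, age, weekly pain intensity at baseline, TMD-specific medication". Expectancy is in neither.

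The Acupuncture Expectancy Scale is "an item measuring the expectation of improvement of illness due to acupuncture treatment", answered on a five-point scale (protocol 8.2.10, SAP 8.3.1.2.7). On timing, protocol 7.2 places it at the end of baseline, and the baseline list in protocol 8.3 says the clinic assessments "must be done before the treatment, including FDI, GCPS, JFLS-20, DASS-21, PSQI, PPT, sEMG, and acupuncture expectancy scale". Table 1 of both documents shows it once, in the week-0 allocation column that also holds randomisation.

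The only stated use is in SAP 6.3, where the "expectation assessment, will be summarized by treatment group for the ITT set". The scale appears in no primary, secondary, exploratory or sensitivity model (SAP 8.2.1, 8.3.2, 8.4.3; protocol 12.6.2 to 12.6.4). No reason is given for leaving it out.

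**The concern.** Several features of this plan make expectancy a natural candidate covariate:

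- The outcome is the patient's own 0-10 pain rating, the comparator is a sham, and the item asks how much the patient expects to improve. Protocol 1.1.2 names placebo response as the possibility that earlier work could not exclude.
- The trial is small, at 30 per arm, and neither document names a stratification factor.
- Sex and age are adjusted for, although the documents offer no more evidence that they are prognostic than they offer for expectancy.
- One covariate already in the model, TMD-specific medication, is disallowed during the study and is an exclusion in the month beforehand (protocol 3.1, 4.3, 5.2). It should be nearly constant and so explain little.

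What is at stake is efficiency. Any outcome variance that expectancy explains beyond the listed covariates stays in the residual and widens the interval. There is also a practical consequence: SAP 6.3 will display expectancy by arm, and if an imbalance shows, an adjustment added at that point would be post hoc and open to challenge.

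**Working it through.** **Inputs from the plan (protocol 12.2, SAP 3.2, SAP 8.2.1).** Pain reductions 3.4±0.3 and 2.9±0.7, so the difference is 0.5; alpha 0.05, two-sided from the stated alternative; 50 evaluable for at least 90% power; 10% loss; 60 randomised.

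**Input not in the plan.** The partial R² of expectancy for week-4 pain change, given the other covariates. It is assumed here over 0 to 0.15.

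**Step 1: the plan's own figure.** Common SD = √((0.3² + 0.7²)/2) = √0.29 = 0.5385. The two-sided normal approximation gives 25 per arm, 50 in total, with power 90.7%. The noncentral t gives 89.6% at 25 per arm. The stated sample size reproduces, so the omission does not make it wrong. After 10% loss, 60 × 0.9 = 54 are analysed, 27 per arm.

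**Step 2: effect of one more covariate on the SE.** Two things happen. The residual variance is multiplied by (1 - R²). The variance of the treatment estimate is inflated by about k = 1 + 1/(n - 8), because with four covariates already in the model the new term is correlated with treatment by chance. The SE ratio is therefore √((1 - R²)·k). With n = 54, k = 1 + 1/46 = 1.0217.

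| Assumed partial R² | (1 - R²)·k | SE ratio | Change in SE |
|---|---|---|---|
| 0 | 1.0217 | 1.011 | about +1% |
| 0.02 | 1.0013 | 1.001 | about 0% |
| 0.05 | 0.9707 | 0.985 | about -1.5% |
| 0.10 | 0.9196 | 0.959 | about -4% |
| 0.15 | 0.8685 | 0.932 | about -7% |

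Simulation (27 per arm; treatment, sex, age and baseline pain, with and without expectancy; 12,000 trials per setting) gives ratios of 1.010, 0.985, 0.959 and 0.932 for R² of 0, 0.05, 0.10 and 0.15. The ratios do not depend on the outcome SD.

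**Step 3: break-even.** The SE falls only if R² exceeds 1 - 1/k = 1/47 = 0.021, a partial correlation of about 0.15. With all 60 analysed, k = 1 + 1/52 and break-even is 1/53 = 0.019, a correlation of about 0.14.

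**Step 4: power.** At SD 0.54 and difference 0.5, simulated power is about 89.7% without expectancy. With it, power is about 89.0%, 90.6%, 91.9% and 93.1% for R² of 0, 0.05, 0.10 and 0.15.

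**Step 5: validity of the planned model.** In the same simulation at R² = 0.10, the model without expectancy has a mean estimate of 0.50 against a true 0.5, and its 95% interval covers 95.0% of the time.

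**The case against.** The strongest reply is that nothing here is broken. The covariate list is pre-specified, agrees between protocol and SAP, and includes baseline pain, usually the first covariate to want. Expectancy is already addressed by design: a matched sham device, blinded participants and assessors, a Bang blinding index and a by-arm summary. Whether a single 1-to-5 item passes the break-even is unknown, and at R² = 0.05 the power gain is under one percentage point. That sex and age are unproven is not in itself an argument for a third unproven covariate. All of this stands, and it is why the point is put as an improvement.

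A reader might infer more, in three ways that the documents do not support.

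- *That the omission biases the result or inflates type I error.* Randomisation protects against this, and Step 5 shows it.
- *That any chance imbalance in expectancy is carried whole into the treatment difference.* It enters only through the slope of pain change on expectancy, and the reported SE and interval already allow for it.
- *That the random shift in the estimate is a further harm, quotable as a share of the planned 0.5.* It is the same variance as the SE loss, plus noise from estimating the slope: the two estimates differ by an SD of about 0.022 even at R² = 0. Large percentages appear only with outcome SDs that are not in the plan.

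On timing, expectancy and randomisation share the week-0 column and their order is not stated. Blinding makes this a small risk, but completion before treatment is not the same as completion before randomisation.

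**Conclusion.** This is an optional efficiency gain worth taking, not a defect. The planned primary analysis is valid as written and its sample size reproduces. Adding the expectancy score costs about 1% in SE if the item carries no information, breaks even near a partial R² of 0.02, and lowers the SE by about 4% at 0.10 and 7% at 0.15. These sizes rest on assumed R² values, on 54 analysed, and on a roughly linear relation. The documents do not show that precision is actually lost, only that it may be. The case for acting is the asymmetry: a small capped cost against a possible gain several times larger, in a small trial of self-reported pain against sham with no named stratification. If the true SD is well above the pilot values, that would affect power far more than this covariate could; it is a separate question.

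**What to change.** Before unblinding:

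1. In SAP 8.2.1 and protocol 12.6.2, add the week-0 Acupuncture Expectancy Scale score (1-5, one linear term) to the covariates of the primary regression. The week-8 pain model follows by reference (SAP 8.4.3, protocol 12.6.4), but it is better to say so.
2. Add it to the 30% and 50% response models, which carry their own covariate list (SAP 8.3.2, protocol 12.6.3), at weeks 4 and 8, so that pain change and pain response are adjusted alike. SAP 8.4.3 does not name the week-8 response analysis and should.
3. State that the scale is completed before randomisation.
4. State whether the other continuous outcomes (jaw movement, GCPS, JFLS-20, DASS-21, PSQI, PPT, sEMG) keep the present four covariates. They are modelled by similarity to the primary analysis, so the change would otherwise pass to them by default.
5. Report the primary model without expectancy as a supporting analysis.

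The cost is a few clauses in two documents, no new data, and one degree of freedom.

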## 3.2 Sample Size and Power Considerations

Based on our pilot study, the reduced pain intensity (VAS score) of TMD patients after 4-week treatment was 3.4±0.3 in the acupuncture group and 2.9±0.7 in the sham acupuncture group. A sample size of 50 patients gives at least 90% power for the study to succeed at an alpha level of 0.05. Assuming a 10% loss rate of follow-up, 30 patients per treatment group were planned for randomization.

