## 3.3 Randomization and Blinding

Eligible participants will be randomly assigned (1:1) to either acupuncture group or sham acupuncture group using an interactive web-based response system (Beijing LNKMED Tech Co., Ltd, Beijing, China) The randomization sequence will be computer generated by an independent statistician who do not participate in the trial. After a participant’s eligibility is determined, a dedicated investigator will access the randomization interface and completed randomization form (each participant’s name, sex, and birthday), and then the random number and group assignment will be displayed on the web interface. Afterwards, this dedicated investigator will inform acupuncturists the randomization.

The participants, outcome assessors, and the statistician will be blinded to treatment assignment. Unmasked personnel will include the dedicated investigator responsible for the randomization module. Because of the nature of the intervention, acupuncturists cannot be blinded, but they will be trained not to communicate with participants or outcome assessors about treatment procedures and responses.

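### The primary regression pools one residual variance, so the per-arm LSM standard errors do not fit the plan's own SDs of 0.3 and 0.7; the difference test is affected only if losses are unequal

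*Combined protocol and SAP*

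**What the plan says.** SAP 3.2 (and protocol 12.2) base the sample size on pilot reductions of "3.4±0.3 in the acupuncture group and 2.9±0.7 in the sham acupuncture group". The SAP adds that "A sample size of 50 patients gives at least 90% power for the study to succeed at an alpha level of 0.05" and, on losses, "Assuming a 10% loss rate of follow-up, 30 patients per treatment group were planned for randomization". The hypotheses in SAP 8.2.1 are two-sided.

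For the primary outcome, SAP 8.2.1 states that "the main analysis was performed using an analysis of linear regression model adjusted for sex, age, weekly pain intensity at baseline, TMD-specific medication". The results to be shown are, first, "The LSM change from baseline with SE was presented for each treatment group", and then the treatment difference with a 95% CI and p-value. Protocol 12.6.2 matches: "The LSM change from baseline with standard error (SE) was presented for each treatment group".

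Neither document mentions robust, Welch-type or arm-specific variances, and the per-protocol sensitivity analysis reuses the same model. SAP 8.2 also contains a sentence naming mixed models, without a covariance structure. It sets out multiple imputation with 10 data sets but does not describe the imputation model.

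**The concern.** The sample-size paragraph and the analysis model make different assumptions about spread. The first uses two clearly unequal SDs. The second, as ordinarily fitted, estimates a single residual SD and gives it to both arms. If the pilot figures are a fair guide, the SE printed beside each arm's LSM change is not that arm's SE: the less variable arm looks less precise than it is, and the more variable arm looks more precise. This holds whether or not the arms end up equal in size.

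A pooled variance can also distort the test of the difference, but only when the arms contribute unequal amounts of information. The plan expects 10% loss, and nothing in it makes the losses equal between arms.

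**Working it through.** **Inputs.** Difference 3.4 − 2.9 = 0.5; SDs 0.3 and 0.7; two-sided alpha 0.05; 90% power; 30 randomised per arm; 10% loss (SAP 3.2 and 8.2.1). The ± is not labelled, so the SD reading is checked first.

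**Reproducing the plan's N.** n per arm = (1.960 + 1.282)² × (0.3² + 0.7²) / 0.5² = 10.51 × 0.58 / 0.25 = 24.4, so 25 per arm and 50 in total. Power at 25 per arm is 90.7% (normal), 89.6% (pooled t) or 89.0% (Welch). The SD reading gives the stated figure. For losses, 50 / 0.9 = 55.6, so 56; the plan takes 60, of whom 54 are expected to be evaluable.

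**Per-arm SE.** Pooled SD = √((0.09 + 0.49)/2) = 0.5385. The model gives 0.5385/√n in each arm; the arm's own SE is SD/√n.

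| n per arm | Model SE, both arms | Acupuncture's own SE | Sham's own SE |
|---|---|---|---|
| 30 | 0.098 | 0.055 | 0.128 |
| 27 | 0.104 | 0.058 | 0.135 |

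The ratios do not depend on n: 0.5385/0.3 = 1.80 (80% too large) and 0.5385/0.7 = 0.77 (23% too small). A simulated covariate-adjusted model at 27 per arm gave 0.105 in both arms under ordinary least squares, and 0.067 and 0.140 under HC3.

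**Difference, equal arms.** The model variance is 2 × 0.29/n = 0.58/n, and the true variance is (0.09 + 0.49)/n = 0.58/n. They are identical. Simulated type I error at 30/30 is about 5.2% (pooled t) or 5.0% (covariate-adjusted).

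**Difference, unequal arms, complete cases.** The expected loss is 60 × 10% = 6.
- All in sham (30/24): model SE = √[((29×0.09 + 23×0.49)/52) × (1/30 + 1/24)] = 0.1415; true SE = √(0.09/30 + 0.49/24) = 0.1530. Simulated type I error is about 7.1%.
- All in acupuncture (24/30): model SE 0.1532, true SE 0.1417. Type I error is about 3.6% (3.9% with covariates).
- Milder splits (acupuncture/sham): 29/25 gives 6.4%, 28/26 gives 5.8%, 25/29 gives 4.2%.

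**Difference, after multiple imputation to 30/30 (10 sets, Rubin's rules).** With a common-variance imputation model, type I error is 7.1% when all six losses are in sham and 3.5% when all are in acupuncture. Using arm-specific SEs on those same imputed data changes little: separate simulations gave 6.6–7.2% and 3.2–3.6%, because at 30/30 the pooled and arm-specific SEs of the difference coincide. Imputing by arm brings both cases back to about 5% (4.8–5.3% across simulations).

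**Sensitivity to the SD ratio.** Take assumed SDs of 0.5 and 0.7 instead. The pooled SD is √((0.25 + 0.49)/2) = 0.608, so the per-arm SEs are 22% too large (0.608/0.5) and 13% too small (0.608/0.7). Complete-case type I error at 30/24 is then 5.8%. With equal SDs the problem disappears.

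**The case against.** Five points can fairly be made for the plan.

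- **The primary test is sound in the expected case.** If six losses fall at random, the chance that all are in sham is C(30,6)/C(60,6) = 1.2%. Averaged over random splits, complete-case type I error is about 5.25%. This stands: a reader might infer that the primary p-value is generally wrong, and the documents do not support that. It needs losses that differ by arm, which nothing in the plan predicts.
- **The ITT analysis imputes back to about 30 per arm.** This is true, but it helps only if the imputation respects the arms' different variances, and SAP 8.2 does not say whether it will.
- **Equal variance is never stated.** It is the default of the named method, not a commitment in words, and the mixed-model sentence could in principle allow arm-specific variances. As written it specifies none, so the default is what would be run.
- **Each arm's own SD and SE appear anyway.** SAP 5.1 requires them among the descriptive statistics. This softens the consequence, but leaves two SEs for one arm that disagree with no explanation.
- **The pilot SDs may not carry over.** They describe unadjusted reductions, the pilot's size is not given, and the model concerns residuals after covariates. This stands and makes the finding conditional.

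Two further inferences also go too far. A reader might conclude that per-arm confidence intervals will under-cover, but the plan reports CIs only for the treatment difference. A reader might also extend the point to the secondary outcomes, but the documents give no SDs for any of them, and the responder analyses are logistic.

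**Conclusion.** The point holds, conditionally. If the residual SDs in the trial differ as the pilot SDs do, the single-variance regression misstates a reported primary quantity in both arms, by +80% for acupuncture and −23% for sham, whatever the losses. The effect on the treatment difference is secondary: none of note with equal arms, and at most about +2 or −1.5 percentage points of type I error if every one of the planned losses falls in the same arm.

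The conclusion assumes that the ± is an SD (supported by the exact match to 50), that the ratio survives covariate adjustment, and that the regression is fitted in its default form. The sample size and power claims are not in question.

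**What to change.** In SAP 8.2.1, with matching text in protocol 12.6.2, state that the LSM SEs and the difference, with its CI and p-value, will be estimated with arm-specific residual variances. HC3 standard errors are an acceptable alternative, though slightly conservative here: simulated type I error was 4.0–4.4%.

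In SAP 8.2, state that multiple imputation will be run separately by arm. This part is needed for the difference test, since robust SEs alone do not correct it on imputed data. In the same edit, settle whether the primary model is the linear regression or a mixed model.

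The cost is a small loss of degrees of freedom: at 27 per arm, power is about 91.3% (Welch) against 91.7% (pooled). N does not change, and almost nothing is lost if the variances prove equal.

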## 8.3 Secondary Efficacy Variables and Analysis

### 8.3.1 Variable Definition

#### 8.3.1.1 TMD Related Data During Treatment Period

##### 8.3.1.1.1 Responder Rates

The following responder rates will be derived: 30% and 50%. A responder is a participant, who achieves a ≥30% reduction or ≥50% reduction in pain intensity at week 4, compared to baseline pain intensity. The population-level summary is the odds ratio of a successful response between two groups.

##### 8.3.1.1.2 Jaw Opening and Movement

In addition to TMD classification, these examination findings are presented as secondary outcomes: pain-free opening, maximum unassisted jaw opening, maximum assisted jaw opening, forward extension and lateral movement (left/right).

Pain-free opening and maximum unassisted opening are measured by the interincisal distance between the maxillary and mandibular reference teeth. In certain settings, repeating the test, if the pain-free opening is less than 30 mm, might be appropriate in order to assess for possible low-range outlying values. Ask the patient about any pain produced by measuring maximum unassisted jaw opening.

Maximum assisted jaw opening is examiner-based. The examiner uses moderate pressure, push the mouth open further, measures the interincisal distance between the maxillary and mandibular teeth.

Lateral excursive measurements are made between the maxillary and mandibular reference midlines, while protrusive excursive measurement is made between the labial surfaces of the maxillary and mandibular reference teeth. For the lateral excursive movements, if the patient is confused about direction s/he should move his or her jaw, touch the ipsilateral side of the face, lip, or even shoulder, and ask the patient to move towards the indicated side. Note that if the mandibular incisors cannot be protruded beyond the maxillary incisors, the value will be negative. If anterior cross-bite situation exists, the field “if negative” on the examination form will be marked. The protrusive movement measured as the distance from the labial surfaces of the maxillary to mandibular incisors, will be recorded as a positive number.

